## Methods/Design

This is a multi-centre, randomised controlled trial. We randomise participants between Mindfulness-Based Cognitive Therapy (MBCT) in addition to Treatment As Usual (TAU), Cognitive Psycho-Education (CPE) in addition to TAU, and TAU alone. In doing so, we stratify participants by (a) research centre (Oxford or Bangor) (b) cohort (c) history of suicidality (none, ideation or suicidal attempt) and (d) whether or not they were taking antidepressants in the 7 days before their first assessment. We originally proposed to stratify by centre, cohort, suicidal behaviour (ideation versus attempt), number of previous episodes of depression (3 or 4 versus 5 or more), and brooding (high versus low scores on a subscale of the Ruminative Response Style questionnaire). However we later changed these, with ethical approval, to reflect the inclusion of participants taking antidepressants or without suicidal ideation. We undertake randomisation by e-mail to the remote randomisation centre at the North Wales Organisation for Randomised Trials in Health (NWORTH) at Bangor University. The randomisation algorithm uses dynamic allocation to protect against subversion while ensuring that each arm of the trial is comparable with respect to the stratification variables. For validation the randomisation e-mail also includes additional information including the participant's date of birth, gender and date of assessment.

We monitor treatment effects over a period of one year. Assessments by trained assessors who are blind to treatment allocation (and whose blindness is checked within each assessment session) take place directly before and after the start of the treatment (T0 and T1), and at three (T2), six (T3), nine (T4) and twelve months (T5) after T1 (see Figure 1 for details of participant flow through the trial). We also offer treatment 'reunions' to participants in both MBCT and CPE at both 6-8 weeks and 6 months after treatment.

**Figure 1 F1:**
[figure not shown]
**Diagram showing participant flow through the trial**. This file includes a diagram which outlines participant flow through the trial, from initial contact with the research team to completion of follow-up assessments.

The study is being conducted in accordance with the WMA Declaration of Helsinki and has been approved by the National Research Ethics Service (Oxfordshire REC C) (MREC 08/H0606/56) and the North Wales Research Ethics Committee.

### The Interventions

The two treatments, MBCT and CPE, both consist of 8 weekly classes of two hours duration. MBCT [4] is a manualised treatment programme that combines training in mindfulness meditation with cognitive therapy techniques which has been adapted for this trial by [name] and colleagues ([name], [name], [name] and [name]) for patients with a history of suicidality. In addition to weekly meetings, we advise participants to spend about an hour per day on home-based practice which includes regular meditation practice and smaller tasks aimed at cultivating mindfulness in everyday life. The rationale of the treatment is based on research suggesting that, in vulnerable individuals, negative thinking patterns can be easily re-activated through only minor events like subtle changes in mood, and that negative mood is often perpetuated through maladaptive habitual patterns of thinking that are characterized by ruminative tendencies and avoidance. Through meditation practice, MBCT aims to help participants to become aware of re-activation of negative thinking at earlier stages and to disengage from maladaptive reactions such as ruminative and avoidant tendencies, which might otherwise ensue. Participants learn to relate to all their experience with openness and acceptance. MBCT has been found to reduce successfully the risk of relapse in patients with three or more episodes of depression in the past. Previous work from our group has shown that cognitive reactivity is particularly pronounced in patients who have suffered from suicidal depression in the past [10], suggesting that MBCT might be particularly helpful as a treatment approach to reduce vulnerability in this group.

The CPE program uses the same format of eight weekly group meetings of two hours. It includes all the elements of the MBCT programme *except *those that are intended to support participants in experientially cultivating mindfulness, namely the meditation practices and the focus in the sessions on experiencing in the present moment. In CPE, as in MBCT, participants are taught about the psychological processes in relapse to depression, and engage in mood monitoring and homework to prevent relapse. They are also taught about the importance of recognising the various elements of experience (thoughts, emotions, sensations and behaviours) and of disengaging from unhelpful patterns of processing such as rumination and experiential avoidance. However, instead of training different ways of relating to these experiences through meditation, CPE *informs *participants about these processes through teacher-led presentations and group discussions. In summary, the main themes of the MBCT and CPE sessions centre on the same subjects and cover the same points; CPE differs from MBCT in avoiding meditation training in the sessions or through home practice. In addition to allowing 'dismantling' analyses of the role of meditation in MBCT, investigating CPE is important as it constitutes an economical alternative treatment.

The four therapists deliver both MBCT and CPE, alternating between the two treatments across the 6 classes that each leads. In week 2 of treatment we ask participants to rate the plausibility of their treatment, not only to assess whether the two treatments are equally plausible, but also to check for therapist treatment allegiance effects. Additionally treatment adherence and competence are being monitored by [name], who developed MBCT [4].

### Sample Size

Two previous trials investigating MBCT for those people who have experienced 3 or more episodes of depression in the past have found that MBCT reduces recurrence from 70% to 39% compared with TAU [5,6]. In this trial we expect that the difference between MBCT and CPE, the other primary comparison, will be smaller. Bockting and colleagues [11] found that Cognitive Behaviour Therapy delivered in groups reduced relapse from 65% (TAU) to 54%; using the hazard ratio derived from these figures, we would expect CPE to reduce rates of relapse or recurrence from 70% to 59%. This difference in effectiveness between CPE and TAU led us to allocate patients between MBCT, CPE and TAU in the ratio 2:2:1. Using a 5% significance level, a final sample of 300 participants (120 MBCT, 120 CPE and 60 TAU) yields 99% power for survival analysis to detect a difference in recurrence between 70% in the TAU control group and 39% in the MBCT group, and 80% power to detect a difference between 39% in the MBCT group and 57% in the CPE group - less than the 59% suggested above.

Although participants are individually randomised, MBCT and CPE, but not TAU, are administered in groups, which means that participants within the same group may influence each other and observations of outcome within groups may not be independent. Reanalysing the two previous trials [5,6], we found that intra-class correlations (ICCs) for recurrence were less than zero, and therefore have little or no effect on power calculations [12]. For depression measures, ICC varied from zero to less than 0.05. MBCT and CPE participants will form 12 therapy groups (clusters) of each type. For secondary analyses on measured outcomes, with 10 respondents per cluster, the proposed sample sizes give 80% power to detect a difference between MBCT and CPE of 0.45 standard deviations if the ICC is 0.05. The smaller sample available for comparing CPE or MBCT with TAU means that the corresponding detectable effect size is 0.53 if the ICC is 0.05. These are generally considered moderate effect sizes. Given a likely attrition rate of 20%, we shall recruit 375 participants to achieve the final sample of 300.

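### The detectable effect of 0.53 SD against TAU does not follow from the stated design; with clustering in the therapy arm only, the same inputs give about 0.48 SD

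*Protocol article*

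**What the plan says.** All of the relevant text is in the Sample Size section of the protocol article.

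- Arm sizes after attrition: "a final sample of 300 participants (120 MBCT, 120 CPE and 60 TAU", from an allocation of 2:2:1.
- Which arms are clustered: "MBCT and CPE, but not TAU, are administered in groups".
- Number and size of clusters: "MBCT and CPE participants will form 12 therapy groups (clusters) of each type", and, a sentence later, "For secondary analyses on measured outcomes, with 10 respondents per cluster".
- Comparison of the two therapies: "the proposed sample sizes give 80% power to detect a difference between MBCT and CPE of 0.45 standard deviations if the ICC is 0.05".
- Comparison of either therapy with TAU: "the corresponding detectable effect size is 0.53 if the ICC is 0.05". The section puts the rise from 0.45 to 0.53 down to the smaller sample in these comparisons.

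The section reports ICCs between zero and just under 0.05 for depression measures in two earlier trials, so 0.05 is the upper end of that range. It gives no formula for either detectable effect and does not say whether the 5% level is one- or two-sided.

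**The concern.** Sharing a class makes outcomes correlated only among people who attend classes. In this design those are the MBCT and CPE participants. The 60 TAU participants are independent observations, and the section says as much. A variance inflation for clustering therefore belongs to the therapy arm of a comparison with TAU and not to the TAU arm.

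The printed 0.53 SD looks too large for that design and close to what results when both arms are inflated. If so, the plan tells its readers that the measured-outcome comparisons with TAU are less sensitive than they are. The figure matters when someone later judges whether a null result against TAU on a scale such as the HRSD or BDI-II is informative.

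**Working it through.** **Inputs, all from the Sample Size section unless marked**

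- n = 120 in the therapy arm (MBCT or CPE) and n = 60 in TAU. Attrition has already been taken off (375 recruited, 300 retained).
- 10 respondents per class, 12 classes per therapy, none in TAU.
- ICC 0.05; power 80%.
- Two-sided 5% level (assumed).

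Design effect: DE = 1 + (10 − 1) × 0.05 = 1.45.
Multiplier: z(0.975) + z(0.80) = 1.960 + 0.842 = 2.8016.
Detectable difference in SD units = 2.8016 × SE.

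**1. The plan's own figure.** With the design effect on both arms:

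SE = √(1.45/120 + 1.45/60) = √0.03625 = 0.1904
Detectable difference = 2.8016 × 0.1904 = **0.533 SD**, which rounds to the printed 0.53.

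**2. The design as described.** With the design effect on the therapy arm only:

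SE = √(1.45/120 + 1/60) = √(0.01208 + 0.01667) = √0.02875 = 0.1696
Detectable difference = 2.8016 × 0.1696 = **0.475 SD**.

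**3. Allowing for few classes.** Take 11 df for the mean of 12 classes and 59 df for TAU. The Satterthwaite value is

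df = 0.02875² / (0.01208²/11 + 0.01667²/59) ≈ 46,

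and the noncentral t calculation gives **0.485 SD**. With 118 to 238 df it gives 0.479 to 0.477.

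**4. Other variants**

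| Variant | Detectable difference (SD) |
|---|---|
| No clustering in either arm | 0.443 |
| Therapy arm only, one-sided 5% | 0.422 |
| Therapy arm only, noncentral t, 11 df | 0.522 |
| Therapy arm only, noncentral t, 10 df | 0.527 |

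To reach 0.53 by the normal formula with TAU uninflated, the therapy-arm design effect would have to be 120 × [(0.53/2.8016)² − 1/60] ≈ 2.29. That is an ICC of (2.29 − 1)/9 ≈ 0.14, nearly three times the stated 0.05.

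**5. Power at the printed effect.** With the SE from step 2, 0.53/0.1696 = 3.126, and Φ(3.126 − 1.960) = Φ(1.166) ≈ **0.878**. A simulation of 12 classes of 10 against 60 independent participants gave 80.2% power at 0.475 SD and 87.8% at 0.53 SD.

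**6. The companion figure, MBCT against CPE.** Both arms are clustered here, so SE = √(2 × 1.45/120) = 0.1555. The normal formula gives 0.436 SD, and a t reference with 22 df (24 classes less 2) gives 0.456 SD. The printed 0.45 lies between them and matches neither exactly.

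**The case against.** **The cause is not proven.** The section shows no formula, so double inflation is an inference. A calculation that leaves TAU uninflated but uses a noncentral t with only 10 df gives 0.527, which also rounds to 0.53. In addition, the normal formula that reproduces 0.53 returns 0.436 for MBCT against CPE, not 0.45, so the two printed figures may have been computed or rounded differently. This stands, and a reader should not take 0.53 as proof that TAU was inflated. It does not rescue the figure, however. A reference with 10 df ignores the 60 independent TAU participants, and for MBCT against CPE it gives 0.483 rather than 0.45.

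**The effect is small and on the safe side.** This also stands. The figure concerns secondary measured outcomes at the top of the reported ICC range. It understates sensitivity, so no comparison is left short of power. The section's description of these effects as moderate reads the same at 0.48 as at 0.53.

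**A reader might infer that the analysis will also treat TAU as clustered, widening the standard errors of every TAU contrast.** The document does not support that. The Analysis section and Appendix 1 refer only to clustering within classes within centres. TAU participants have no classes, and no text assigns them to any. How TAU is coded in the random-effects structure is detail that an article may leave to a fuller plan.

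**Conclusion.** The point holds as an arithmetical inconsistency within one paragraph. On the stated inputs the detectable difference for MBCT or CPE against TAU is about 0.475 SD (0.485 with Satterthwaite df), not 0.53. The printed value is too high by about 12% relative to 0.475 (0.53/0.475 = 1.116), or about 9% relative to 0.485 (0.53/0.485 = 1.093). At 0.53 SD the power is about 88% rather than 80%.

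This rests on a two-sided 5% test, classes of exactly 10, ICC 0.05 and independent TAU participants. A one-sided test would widen the gap (0.422 SD). Inflation of the TAU arm is the most likely cause, not an established one.

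Nor should the point be read as a fault in the trial's size. The 99% and 80% power figures for relapse come from survival calculations that do not use this number, and the totals of 300 and 375 do not depend on it.

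**What to change.** In the Sample Size section, restate the detectable effect for MBCT or CPE against TAU as about 0.48 SD at 80% power and ICC 0.05, and say that the design effect of 1.45 applies to the therapy arm only. Add that the test is two-sided, if it is. If 0.53 came from a different method, state that method and show that it also yields the 0.45 for MBCT against CPE.

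The cost is one number and a clause. The corrected figure favours the trial, and neither recruitment nor the primary analysis changes.

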### Referral and recruitment

We recruit participants through advertisements in the community, in clinics and GP surgeries, as well as through referrals from GPs and mental health clinicians, whom we inform about the study through letters and talks at professional meetings. Recruiters working on the trial contact people who respond to advertisements, GPs or mental health clinicians and explain the study to them. If they express interest, a recruiter screens them for the main inclusion and exclusion criteria of the trial using a standardised checklist. The recruiter sends the information sheet to eligible participants, and, if they are willing to participate, invites them to an assessment session at the trial site in Oxford or Bangor.

### Inclusion criteria

Principal inclusion criteria for the study are:

1) Age between 18 and 70 years, because depression in old age is related to different factors than depression in earlier stages of life [13,14].

2) Meeting enhanced DSM-IV criteria for a history of Recurrent Major Depression, namely a history of at least three episodes of depression, of which two must have occurred within the last five years, and one within the last two years [15]. Although previous suicidality is recorded in detail, thus facilitating stratification, prior experience of suicidality is not a prerequisite for participating in the trial.

3) Meeting the NIMH guidelines for recovery or remission at the time of baseline assessment. Potential trial participants are deemed *not *to be in recovery or remission, and hence *ineligible*, if they report at least one week during the previous 8 during which they experienced *either *a core symptom of depression (depressed mood, anhedonia) *or *suicidal feelings and at least one other symptom of depression, which together are not attributable to bereavement, substances or medical condition, but are impairing functioning.

4) Giving informed consent.

5) Consent received from the participant's General Practitioner.

### Exclusion criteria

We exclude potential trial participants if one or more of the following apply:

1) They have a history of schizophrenia, schizoaffective disorder, bipolar I disorder, current severe substance abuse, organic mental disorder, pervasive developmental delay, a primary diagnosis of obsessive-compulsive disorder or eating disorder, or regularly harm themselves.

2) They report a positive continuing response to CBT.

3) They receive psychotherapy or counselling more than once per month

4) They cannot complete the baseline research assessment, for example through difficulties with English, visual impairment, or cognitive difficulties.

### Assessment of Eligibility and Baseline Measures

Before the first assessment session, researchers explain the trial to participants and give them the information sheet again. After they have had opportunity to discuss any questions, the researchers seek written informed consent after telling participants that they have the right to withdraw from the research at any time.

We ask consenting participants to provide information about their socio-demographic background and assess their eligibility in more detail using semi-structured clinical interviews and self-completed questionnaires. The researchers assess current and past diagnostic status using the Structured Clinical Interview for DSM IV (SCID [16]), the Suicide Attempt Self Injury Interview (SASII [17]) and the Hamilton Rating Scale for Depression (HRSD[18]). They ask participants to complete a crisis card, and to describe past and current treatments for depression and past meditation and yoga experience.

They then ask participants themselves to complete the Beck Scale for Suicide Ideation (BSS-current [19] and worst [20]), the Mini International Neuropsychiatric Interview (MINI) Suicidality Tracking measure [21], the Beck Depression Inventory (BDI-II [22]) to assess severity of current symptoms of depression, the Beck Hopelessness Scale (BHS [23]) to measure current levels of hopelessness, a questionnaire assessing occurrence of life events [24], a measure of global functioning (Clinical Outcome Routine Evaluation, CORE [25]), a measure of general quality of life (Euro-QOL EQ-5D [26]), a questionnaire assessing history of trauma (Childhood Trauma Questionnaire, CTQ [27]), and two short measures of anxiety and depression symptoms (GAD7 [28] and Patient Health Questionnaire, 9-item version, PHQ9 [29]). If participants meet all inclusion and none of the exclusion criteria for the study, they enter the study and are invited to the second pre-treatment assessment session.

The second pre-treatment assessment asks participants to complete several cognitive tasks and to fill in several self-completed measures assessing factors related to cognitive vulnerability for depression. The cognitive tasks include the Autobiographical Memory Test (AMT [30]), in which participants are given cue words and asked to remember specific events from their life. They also complete two short tests of executive capacity, the Number Generation Task [31], in which they generate sequences of numbers within given ranges, and the Baddeley Dual Task [32]. Questionnaires at this assessment include measures of: mindfulness (Five Factor Mindfulness Questionnaire, FFMQ [33]), self-compassion (Self-Compassion Scale, CS [34]), rumination (Ruminative Responses Subscale of the Response Styles Questionnaire, RSQ [35]), dysfunctional attitudes (Dysfunctional Attitudes Scale, DAS [36]), acceptance (Acceptance and Action Questionnaire, AAQ [37]), suicidal cognitions (Suicide Cognitions Scale, SCS, 37), suicidal thinking (Suicidal Thoughts Questionnaire), self-discrepancies (Self-Guides Questionnaire [38]) and frequency of thought suppression.

### Informed Consent

We seek informed consent on two occasions, the first before assessing eligibility, already described. Secondly, we ask participants who are eligible and have finished the second pre-treatment assessment to renew their consent *before *they are randomised to one of the treatments. Participants again receive full information about the study and the opportunity to ask any questions about the trial. We remind them that they can withdraw from the trial at any time without affecting their usual care. The researchers check that participants understand all aspects of the trial. If they agree to enter the trial, they complete another three copies of the consent form. One copy of the completed consent form is for the participant, one for the local research team, and the last for the central research team in Oxford.

### Outcome Measures

The primary outcome measure of the trial is the time to relapse or recurrence meeting DSM-IV criteria for Major Depression, which we assess by the Structured Clinical Interview for DSM-IV (SCID). We assess the occurrence of relapse or recurrence at all follow-up assessments, and treat 'return to treatment' as a relapse or recurrence if, in the judgment of a blind assessor, the participant has experienced exacerbation of symptoms that would have met the criteria for Major Depression in the absence of immediate treatment. In addition to diagnostic status, we assess severity of depression and hopelessness at all time points, using several interview and self-completed measures including the Hamilton Rating Scale for Depression, the Beck Depression Inventory and the Beck Hopelessness Scale. These quantitative measures strengthen the dichotomised outcome of diagnosis. The statistical analysis plan in Appendix 1 gives further details.

We assess cognitive measures relevant to risk of relapse or recurrence, namely mindfulness, self-compassion, rumination, self discrepancy, autobiographical memory and executive capacity before and immediately after treatment and at the end of the follow-up. We shall use these measures in explanatory analysis of factors that mediate or moderate efficacy.

### Pre-Class Interviews

We tell all participants the outcome of randomisation by letter (in addition to email or telephone if requested). We invite those allocated to MBCT or CPE to meet the therapist running their class and those in TAU to meet another member of the research team. These meetings take between 1 and 1.5 hours and either prepare participants for classes, including discussion of ways of coping with barriers to treatment, or discuss procedures for keeping in touch with participants not in classes.

Each week of the eight-week treatment phase, we ask all participants to complete a brief set of tracking questionnaires. These include short ratings of tendencies to ruminate, occurrence of intrusive thoughts, thought suppression, and the PHQ9 and GAD7 scales for assessing symptoms of depression and anxiety. At the start of the second class we also ask participants receiving MBCT or CPE to rate the plausibility of their treatment. Finally participants receiving MBCT complete a short diary documenting homework and practice completed throughout the week.

